### Randomization and blinding

A randomization schedule will be generated and incorporated into an electronic Randomization and Trial Supplies Management (RTSM) system. The treatment group will be assigned as the site randomizes the participant. In phase 2A of the trial, as shown in Fig 2, each participant will be randomly allocated in a 1:1:1 ratio into one of the 3 groups: 1200 mg/d benfotiamine, 600 mg/d benfotiamine or placebo. At the dose decision point that ends phase 2A, all participants enrolled in the two phase 2A active dose arms will receive a new supply of benfotiamine at the selected highest tolerable dose for phase 2B. An unscheduled visit at the start of phase 2B may be required to replace IP supply in all active participants once the phase 2A dose selection is made. Newly enrolled participants will be randomized 1:2 active arm to placebo arm until parity is achieved between numbers of active and placebo arm participants (approximately 150 participants total), randomized 1:1 thereafter (approximately 100 participants). In both phases of the trial, the randomization will be stratified by site.

Participants and study personnel will be blinded to both treatment arm and dosage. There will be provisions for the site Principal Investigator (PI) to unblind treatment assignment in consultation with the ADCS Medical Monitor only in the case of an emergency.

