#### Phase 2B exploratory endpoints

Exploratory endpoints in phase 2B include within-participant longitudinal change between active arm and placebo in: 1) cranial MRI volumetric measures of hippocampal, whole brain, and ventricles, as well as regional cortical thickness, 2) scores on the Neuropsychiatric Inventory (NPI) [32], 3) scores on neuropsychological test measures administered remotely and in-person, 4) ADAS-Cog-Exec [33] scores, 5) levels of plasma biomarkers Aβ42/Aβ40 ratio, p-tau217/np-tau217 ratio, p-tau217, total tau, p-tau 231, NfL and GFAP, 6) AGE levels measured in plasma as an exploratory endpoint of PD, and 7) PK (plasma thiamine, thiamine esters in whole blood including ThDP and ThMP, and erythrocyte transketolase activity) relationships to PD biomarkers (AGE) and clinical outcome measures.

AGE levels will be measured on plasma samples and four AGE by mass spectrometry (N(6)-carboxymethyl-lysine (CML), pentosidine, N(6)-carboxymethyl-lysine (CEL), methylglyoxal-derived hydroimidazolone) will be quantified to measure all specific modes of action of benfotiamine.

Neuropsychological measures administered in-person include the Boston Naming Test (30-item) [34], the Trail Making Test (Parts A and B) [35], and WAIS-R Digit Symbol Substitution [36]. Neuropsychological measures administered remotely (via video-call) include Immediate and Delayed Recall from the Rey Auditory Verbal Learning Test [37], Number Span Forward and Backward [38], Category Fluency [39] and Letter Fluency [39]. Remote measures will be administered over videoconference-call within 10 days after each in-person visit (baseline, week 24, week 48, and week 72). Participants will use their own interactive video capable devices for the remote assessments, although study-provided devices will be available, as needed.

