#### Phase 2B

The primary analyses will be performed on the modified intent to treat (mITT) population which includes all randomized participants who took at least one dose of the study medication, have a baseline assessment of the co-primary efficacy endpoints, and have at least one efficacy evaluation following baseline. The primary analysis will be the same for each co-primary endpoint (CDR-SB and ADAS-Cog13) and will test within subject change in the measure as the outcome in a mixed effects repeated measures model using all available outcomes in the mITT population with no imputation for missing data. Fixed effects in the model will be *APOE* status, baseline value of the outcome measure, baseline by visit-week interaction term, treatment group, visit-week, and visit-week by treatment group interaction. The approach will be maximum likelihood. Visit will be treated as a categorical variable. The covariance structure will be specified as follows: the random effects will include site and subject. The within-subject covariance will be unstructured. If needed, sites will be pooled (in order of enrollment, starting from minimum enrollment) so that there is a minimum of 5 participants per site. If the model fails to converge at the default setting for the software used, then site will be changed to a fixed effect, and if this model does not converge, site will be removed from the model. If the model does not converge, the following structures for the within subject covariance will be fit, sequentially, until the structure is found that results in convergence of the model: Huynh-Feldt, Toeplitz, Autoregressive (1), and Compound Symmetry. A sandwich estimator will be utilized to estimate the variance estimates, and degrees of freedom will be calculated using the between-within method. The primary endpoint will be tested using model-adjusted least squares means at the week 72 visit. Point estimates, standard errors, two-sided 95% confidence intervals, and p-values will be presented.

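### The primary mixed model lists a random subject effect beside an unstructured within-subject covariance; the subject term is redundant, and no fallback step removes it

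*Protocol article*

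**What the plan says.** The Phase 2B subsection of Statistical analyses fixes one model for both co-primary endpoints, CDR-SB and ADAS-Cog13. It is a maximum-likelihood repeated-measures model for change from baseline that uses the observed data without imputation. "Visit will be treated as a categorical variable". On the covariance the text reads "the random effects will include site and subject. The within-subject covariance will be unstructured".

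The trigger for the fallback is worded "If the model fails to converge at the default setting for the software used". The first remedy concerns site alone: "then site will be changed to a fixed effect, and if this model does not converge, site will be removed from the model". Where convergence still fails, the within-subject structure is replaced in the order "Huynh-Feldt, Toeplitz, Autoregressive (1), and Compound Symmetry", stopping at the first that converges. No step removes the random subject effect. For inference, "A sandwich estimator will be utilized to estimate the variance estimates, and degrees of freedom will be calculated using the between-within method". The secondary endpoints follow the same strategy.

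Randomization and blinding adds: "In both phases of the trial, the randomization will be stratified by site".

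**The concern.** A random subject intercept and an unstructured within-subject matrix both describe the correlation between visits of one participant. If the second is fully general, the first has nothing left to explain, and the data cannot separate the two.

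What is at stake is which model is the confirmatory one. If the software reports the redundancy as non-convergence, the written rule alters site, which has no part in the problem and is the factor used to stratify randomization. It then tries other covariance structures with the redundant term still in place. One paragraph could thus lead to a site-adjusted unstructured model or to a model without site and with a much simpler covariance, with software behaviour deciding between them. With 20% dropout planned and no imputation, the point estimate relies on the covariance model; the sandwich estimator repairs standard errors, not the estimate.

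**Working it through.** **Inputs.** The random effects, covariance, fallback order and estimator come from Statistical analyses, Phase 2B. The article names in-person visits under Phase 2B exploratory endpoints, "within 10 days after each in-person visit (baseline, week 24, week 48, and week 72", so t = 3 post-baseline visits is used. The schedule figure is not shown, so t = 4, 5 and 6 were checked as well.

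**The plan's own figure.** Power calculation and sample size gives 203 per arm for d = 0.38, 5% drop-in, 20% dropout and 90% power per endpoint. With two-sided 5% assumed (the power paragraph does not state alpha), n = 2(1.960 + 1.282)² / (0.38 × 0.95)² = 2 × 10.51 / 0.1303 = 161.3, so 162 evaluable; 162 / 0.80 = 202.5, so 203. This reproduces and does not depend on the covariance specification.

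**Algebra.** With subject variance s and within-subject matrix R, the marginal covariance is V = sJ + R, where J is the all-ones matrix. Only V enters the likelihood. Replace s by s − c and R by R + cJ: V is unchanged. The question is whether R + cJ stays in the same family.

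- Unstructured: yes; every element is free.
- Huynh-Feldt: yes. Diagonal v_i becomes v_i + c, and off-diagonal (v_i + v_j)/2 − λ rises by exactly c with λ unchanged.
- Toeplitz: yes; c is added to each lag band.
- Compound symmetry: yes; c is added to the common covariance.
- AR(1): no. With variance σ² and correlation ρ, staying AR(1) needs (σ²ρ + c)² = (σ² + c)(σ²ρ² + c), which reduces to c(1 − ρ)² = 0. For ρ < 1 only c = 0 works.

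**Numerical check.** Rank of the Jacobian of V with respect to the parameters, t = 3:

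| Structure plus random subject | Parameters | Rank | Identifiable |
|---|---|---|---|
| Unstructured | 7 | 6 | no |
| Huynh-Feldt | 5 | 4 | no |
| Toeplitz | 4 | 3 | no |
| AR(1) | 3 | 3 | yes |
| Compound symmetry | 3 | 2 | no |

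The pattern is the same for t = 4, 5 and 6 (unstructured: 11 against 10, 16 against 15, 22 against 21). Without the subject effect, the unstructured model at t = 3 has 6 parameters and rank 6, with the same V.

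**Flatness.** On simulated data (n = 325, t = 3) the log-likelihood was −2392.97 at subject variances 0, 1, 2, 3 and 4, with R positive definite throughout.

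**Following the fallback.** Making site fixed, or removing it, leaves sJ + R untouched. If the redundancy is what stops the fit, both site steps fail too, as do Huynh-Feldt and Toeplitz. AR(1) plus subject is the first identifiable stop. It imposes one variance at all visits.

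**Size if that stop is reached.** Assumed CDR-SB change SDs are 0.9, 1.35 and 1.74 (only 1.74 is in the article), with 18–24% dropout at random. The true difference is 0.38 × 1.74 = 0.66 in absolute value. Large-sample fits in two dropout scenarios gave:

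- Unstructured −0.661, AR(1) plus subject −0.657: shift 0.004 / 0.661 = 0.6%.
- Unstructured −0.663, AR(1) plus subject −0.646: shift 0.017 / 0.663 = 2.6%.

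AR(1) plus subject fitted a single SD of 1.31–1.33 and understated the week-72 decline within each arm by 2–8%, most of which cancels between arms. In 600 simulated trials of 203 per arm (about 18% dropout, no site effect), mean differences were −0.674 and −0.668, and significance changed in 0.7% of trials.

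**The case against.** The strongest reply is that redundancy is not non-convergence. A flat ridge still has a maximum, and every point on it gives the same marginal covariance and so the same week-72 estimate and standard error. In a check with 203 per arm, three visits and about 16% dropout, the unstructured model plus random subject converged in 1,450 of 1,450 datasets; the estimate matched the plain unstructured model within 3e-6 and the standard error within about 1e-7. This stands, but for one optimiser, without site or covariates; other software may stop. No software run that fails has been shown.

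A reader might therefore infer too much: that the primary p-value always depends on how software treats the singularity, or that the trial will end with an AR(1) analysis without site. The article does not support either. A zero subject variance is the plain unstructured model, and a Hessian warning can accompany the same fixed effects. Only declared non-convergence starts the fallback. The printed list also ends at compound symmetry; AR(1) is the stopping point only if the earlier structures fail and subject is kept throughout.

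Nor is serious harm to the test shown. In the same kind of simulation, rejection under the null was 5.7% (unstructured) against 5.5% (AR(1) plus subject), and 95.9% against 95.4% with an effect; decisions agreed in 98–99% of datasets. The cost of losing site has not been quantified, and small sites are pooled before site is altered.

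Finally, subject may have been meant only as the blocking unit of the repeated measures, and the model code may sit in a SAP that is not shown. That makes a slip of wording plausible, but the printed text lists subject as a random effect.

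**Conclusion.** The specification is wrong as written, at moderate importance. That the random subject effect is redundant with the unstructured, Huynh-Feldt, Toeplitz and compound-symmetry structures is exact algebra and needs no assumption about the data. That the fallback alters site first and never removes the subject term is plain from the text.

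The consequence is conditional on software. It ranges from none to a shift of under 3% in the between-arm difference, the latter resting on assumed SDs at weeks 24 and 48 and on dropout at random. The case for correction is that the primary model of both co-primary endpoints should be well defined, not that a large bias has been shown. The sample size stands.

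**What to change.** Delete subject from the random effects and keep site as the only one, so that the within-subject matrix alone carries the correlation between a participant's visits. For example: *Site will be a random effect. Correlation among repeated measures within a participant will be modelled by an unstructured covariance matrix.* State that the Huynh-Feldt, Toeplitz and compound-symmetry fallbacks are also fitted without a random subject effect. For AR(1) either choice is identifiable, so say which is meant.

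Simplifying the covariance before removing site is a reasonable option, since site is the stratification factor, but the algebra does not require it. A different optimiser sequence or other heterogeneous-variance structures are likewise matters of preference; Huynh-Feldt already allows visit-specific variances.

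The cost is a change of wording in the protocol, and in the SAP if it repeats the text, made before unblinding. Sample size and data collection are unaffected.

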### Power calculation and sample size

Table 3 shows that with a total sample size of n = 406 (203/arm), a 20% dropout rate, and a 5% drop-in rate from the placebo arm to active treatment, the trial will be powered at 80% overall (90% on each endpoint separately) to detect a difference between arms, corresponding to a Cohen’s d effect size of 0.38 which represents a small to moderate effect size. This would be a reasonable and clinically relevant difference between arms on each co-primary endpoint, and would be commensurate to the 35% to 40% amelioration of decline seen in the placebo arm of the recently completed phase 2 trial of donanemab in patients with early AD [40], and would correspond to an absolute difference between arms on the CDR-SB of 0.7 points (assumed SD = 1.74) and of 1.7 points (assumed SD = 4.35) on the ADAS-Cog13.

**Table 3 pone.0302998.t003:** Sample sizes which achieve 90% power for given effect sizes (Cohen’s D; difference between the 2 arms), assuming 20% dropout and assuming drop-in rates of 5% and 10%.

drop-in rate	effect size	n / arm
5%	0.35	239
**5%**	**0.38**	**203**
5%	0.40	183
10%	0.35	266
10%	0.38	226
10%	0.40	204

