Mean changes in the secondary endpoints from baseline to week 72 will be compared between arms using the analysis strategy outlined above. To control alpha over the primary and all secondary endpoints, an overall hierarchical gatekeeper strategy will be used, similar to the primary analysis. First, if the primary analysis is not significant, then the secondary endpoints will not be formally tested, and will be presented using exploratory summary statistics only (means and uncorrected 95% confidence intervals by arm and for the difference between arms).

No claims of statistical significance will be made. However, if the primary analysis is significant, the secondary endpoints will be tested in the listed order in hierarchical manner, each using an alpha of 5%. Once a secondary endpoint has failed to attain the prespecified 5% significance level, the remaining secondary endpoints will be presented as exploratory only. This strategy will maintain the overall familywise significance level for the primary and all secondary endpoints at 5%. Exploratory analyses will be detailed in the statistical analysis plan, and will generally be similar to the primary and secondary analyses.

Safety and tolerability data as well as demographic data for the safety population will be summarized in tabular and/or graphical format for each treatment group. The incidence of all laboratory test abnormalities and the median changes from baseline will be tabulated by treatment regimen and time point.

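### Read literally, a failed co-primary analysis replaces the mixed-model estimate of the secondary efficacy endpoints with descriptive means; the gate should control claims of significance, not the estimator

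*Protocol article*

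**What the plan says.** All passages are in the Protocol article, Statistical analyses, Phase 2B, unless noted.

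- **Primary method.** Each co-primary endpoint is analysed in a "mixed effects repeated measures model using all available outcomes in the mITT population with no imputation for missing data". The model has baseline, baseline-by-visit, APOE status, treatment, visit and treatment-by-visit terms, with site and subject as random effects. On the estimate itself: "The primary endpoint will be tested using model-adjusted least squares means at the week 72 visit".
- **Secondary endpoints, general rule.** "Mean changes in the secondary endpoints from baseline to week 72 will be compared between arms using the analysis strategy outlined above".
- **Secondary endpoints after a failed primary analysis.** They receive no formal test; instead they "will be presented using exploratory summary statistics only (means and uncorrected 95% confidence intervals by arm and for the difference between arms". Significance is not claimed for them.
- **After a failed step in the hierarchy.** The text says only that "the remaining secondary endpoints will be presented as exploratory only", with no description of the statistic.
- **Exploratory analyses.** They are left to the statistical analysis plan and "will generally be similar to the primary and secondary analyses".
- **Power calculation and sample size.** The calculation assumes 203 per arm, "a 20% dropout rate" and 5% drop-in, with 90% power per endpoint and 80% overall at d = 0.38.
- **Phase 2B secondary efficacy endpoints.** These are the change from baseline to week 72 on ADCS-ADL-MCI and on MoCA.

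**The concern.** A gatekeeping procedure settles whether a result may be called significant. It gives no reason to estimate the same quantity differently according to the primary p-value. The closed-gate sentence restricts the display to summary statistics and names means without qualification, whereas the primary paragraph speaks of model-adjusted least squares means. On its literal reading, the week-72 difference on ADCS-ADL-MCI and MoCA would be a difference of descriptive means. It would not be adjusted for baseline, APOE or site, and it would ignore the earlier visits of people who left.

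The stake is the quality of an estimate, not an error rate. After a failed or split co-primary result, the secondary estimates would come from a different method than the co-primary estimates beside them. They would be less precise, and they would be exposed to dropout that differs between arms. The model handles such dropout when it depends on observed data.

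**Working it through.** **1. The plan's own sample size.** Effect after 5% drop-in: 0.38 × 0.95 = 0.361. Evaluable n per arm = 2 × (1.960 + 1.282)² / 0.361² = 161.3, so 162. With 20% dropout: 162 / 0.80 = 202.5, so 203. The stated 203 is reproduced. Power at 203 per arm is 90.2% per endpoint.

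**2. How often the closed-gate branch is taken.** The 80% overall figure, built from 90% per endpoint, implies that both co-primaries must succeed. If they are independent, joint power is 0.902² = 0.814, so the branch is taken 18.6% of the time under the planned effect (20% by the stated power). With no effect on either endpoint, both succeed less than 5% of the time, so the branch is taken more than 95% of the time.

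**3. The passages side by side.**

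| Situation | Estimator named |
|---|---|
| Primary endpoints | Model-adjusted least squares means, week 72 |
| Secondary, general rule | Same strategy as the primary |
| Secondary, primary failed | Summary statistics only: means and intervals; type of mean not stated |
| Secondary, after a failed step | None; exploratory only |

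The third row is a specific rule following a general one, and it does not repeat the model. That makes descriptive means the literal reading.

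**4. Precision, if raw means were used.** Baseline adjustment alone, with complete data, gives a standard error ratio (raw to adjusted) of 1/√(1 − r²), where r is the correlation of baseline with change:

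- r = 0.10: 1/√0.99 = 1.005
- r = 0.30: 1/√0.91 = 1.048
- r = 0.45: 1/√0.7975 = 1.120

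Recovering information from the earlier visits of people who drop out adds to this. Two simulation set-ups at 203 per arm, with three post-baseline visits and dropout near 20%, compared the difference in observed week-72 mean change with a likelihood estimate adjusted for baseline.

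- *Set-up A*: 4,000 trials per scenario; visits at weeks 24, 48 and 72 with inter-visit correlations 0.55 to 0.75; r = 0.10, 0.30 or 0.45; log-odds of dropout +0.8 per SD of last observed worsening (1.2 as a check). Standard error ratio 1.02 to 1.15, and about 1.07 at r = 0.30. Since 1 − 1/1.07² = 0.127, a ratio of 1.07 is like losing about 13% of the participants.
- *Set-up B*: 1,500 trials per scenario; adjacent-visit correlation 0.6; realized dropout 18% to 25%. Ratio 1.01 to 1.03 at r = 0, 1.05 to 1.08 at r = 0.3, and 1.13 to 1.20 at r = 0.5.

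**5. Bias in the arm difference, if raw means were used.**

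| Dropout | Raw means | Model |
|---|---|---|
| Random (B) | about 0 | 0.005 SD or less |
| Outcome-related, same in both arms | 0 to 0.02 SD (B); up to 0.03 SD (A) | 0.005 SD or less |
| Outcome-related, 25% vs 15% (A) | 0.03 to 0.06 SD | below 0.005 SD |
| Outcome-related in one arm, random in the other (B) | 0.07 to 0.10 SD | 0.005 SD or less |

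Against d = 0.38, a bias of 0.03 to 0.06 SD is 8% to 16% of the planned effect (0.03/0.38 and 0.06/0.38). It favours the arm that loses more decliners. In the 25% vs 15% setting, the raw 95% interval covered 91% to 95%.

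**6. What is assumed.** The documents give no correlations and no dropout mechanism for ADCS-ADL-MCI or MoCA, and one dropout rate rather than a rate by arm. The assessment schedule for these two scales is in a figure that is not shown, so the visit weeks are also an assumption.

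**The case against.** A reader might infer that the plan definitely drops the mixed model and uses raw completer means whenever the primary p-value misses, and that the reported effects are therefore biased by dropout. The documents do not support a claim that firm.

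- The text never says raw, observed-case, completer or unadjusted, and it never says the model is abandoned. In a sentence about alpha control, 'uncorrected' most naturally means without multiplicity correction. Least squares means with 95% intervals and no p-values would satisfy the wording.
- The general rule for secondary endpoints carries no condition. The line that exploratory analyses "will generally be similar to the primary and secondary analyses" could extend the model to endpoints relabelled exploratory, although it more naturally concerns the separate list of exploratory endpoints.
- Bias needs dropout that works differently by arm. The document gives a single 20% rate. Early discontinuation also lets people who stop treatment stay in follow-up, so stopping need not mean a missing week-72 value.
- Nothing is tested in this branch, and the analysis plan, which is not shown, may settle the matter.

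Most of this stands, and it limits the point to unclear wording with a conditional consequence. It does not remove the point. The protocol itself fixes the closed-gate display, in words that fit descriptive tables better than model estimates. An analysis plan using least squares means would have to interpret that sentence generously, and choosing between the readings after unblinding would be data-dependent.

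**Conclusion.** The concern holds in a limited form. The closed-gate rule, taken literally, departs from the model that the same section assigns to the secondary endpoints. Least squares means are a possible reading but are not stated.

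If raw means were used, the more certain cost is precision: a standard error about 2% to 15% larger for an assumed baseline-change correlation of 0.10 to 0.45. Bias is conditional: up to about 0.02 to 0.03 SD with equal dropout, and about 0.03 to 0.06 SD with an assumed 25% vs 15% outcome-related split. The 0.07 to 0.10 SD result needs dropout to be outcome-related in one arm only, which nothing in the document indicates.

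Familywise error, the primary analysis and power are unaffected. The point should still be settled now, because the branch is taken about 20% of the time under the planned effect and more than 95% of the time under none.

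**What to change.** Replace the closed-gate description with wording such as:

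> Whatever the result of the primary analysis, each secondary efficacy endpoint is reported with the week-72 least squares mean change by arm, the difference between arms and its 95% confidence interval without multiplicity correction, from the same mixed model as the primary endpoints. When the gate is closed, no p-value is given and no significance is claimed.

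Use the same wording for endpoints that follow a failed step in the hierarchy, so that both closed-gate cases read alike. Observed means may be added as a descriptive table.

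The cost is one sentence in the protocol, mirrored in the analysis plan. The model is already planned for the open-gate case, so no further data or participants are needed and the familywise error rate does not change.
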